#### Hamilton anxiety rating scale

The severity of anxiety is often determined by psychological scales. The Hamilton Anxiety Scale (HAMA) is one of the first rating scales to measure the severity of perceived anxiety symptoms. It is considered one of the most widely used rating scales and has been translated into Cantonese (51). A structured interview guide contains a 14-item Hamilton Anxiety Rating Scale of general anxiety, which is rated on a 5-point scale and ranged from 0 (none) to 4 (very severe) by the interviewer.

#### Generalized anxiety disorder scale

Several different types of anxiety disorders have been found in PSA. GAD seems to be the most common type (11). The 7-item Generalized Anxiety Disorder Scale (GAD-7) is commonly used to monitor anxiety symptoms. The reliability and validity of GAD-7 have been well-documented (52). A diagnostic meta-analysis in East Asian samples concluded that given the brevity, sensitivity, and specificity of the questionnaire reported, GAD-7 can be well-utilized to identify people with GAD (53).

### The secondly outcome

The secondary outcomes are the physical recovery and daily quality of life for patients with PSA, which are evaluated by the National Institute of Health stroke scale (NIHSS) and the Modified Barthel Index Scale (MBI). Besides, secondary outcomes will be obtained using ELISA and fMRI scanning. ELISA will be used for quantitative analysis of the content of CORT and ACTH in serum.

#### National institute of health stroke scale

Stroke severity is measured using the National Institute of Health Stroke Scale (NIHSS) (54). There is a 15-item neurologic examination in the NIHSS that is used to assess stroke symptoms. The items are graded from 0 to 42 on an ordinal scale, with higher scores indicating greater severity.

#### Modified barthel index scale

The Modified Barthel Index (MBI) contains ten basic aspects assessing functional independence related to self-care and mobility (55). Each item is divided into five levels, and the level represents different degrees of independence. The lowest level is 1 and the highest is 5, while the higher the level, the greater the independence. The normal score is 100.

#### Enzyme-linked immunosorbent assay

The concentration of ACTH and CORT levels in plasma are measured with commercially immunosorbent assay (ELISA) kits (56). All procedure is conducted according to the manufacturer's instructions. We first measure the absorbance of each sample at 450 nm. Then, a standard curve will be drawn, with the absorbance as the ordinate and the corresponding standard concentration as the abscissa. A regression equation from the standard curve will be used to calculate the concentration of CORT and ACTH in each sample.

#### Functional-MRI

Each subject underwent an fMRI scanner with a head orthogonal coil for fMRI data acquisition before and after acupuncture treatment. Before the scanning, participants should adjust the environment on the bed for at least 5 min to help calm down. The subject must hold still and not think systematically or fall asleep. To keep away from the scanner noise and optical disturbance, eyeshades and earplugs are put on. To keep the head from moving, foam pads are used. The scan will be performed in the following order. The position of the image involving the entire brain is structurally acquired by resting-state blood oxygenation level-dependent (BOLD) imaging and echo-planar imaging sequence (57). Then, a three-dimensional (3D) structure is included in the brain volume imaging sequences by capturing a high-resolution image of the entire brain scan (58). The parameters of each sequence scan are listed in Table 3.

**Table 3 T3:** Scanning parameters.

**Sequence**	**TE (ms)**	**TR** **(ms)**	**Depth (mm)**	**Interval** **(mm)**	**Vision (mm^2^)**	**Matrix**
Bold	30	2000	4	0	240 × 240	64 × 64
3D-BRAVO	3.1	8.1	1	0	256 × 256	256 × 256

TE, time of echo; TR, time of repetition; BOLD, blood oxygenation level-dependent; 3D-BRAVO, three-dimensional brain volume imaging.

### Incidence of adverse events

Although acupuncture is a relatively safe treatment with a low risk of adverse events (AEs), at each acupuncture treatment, study acupuncturists will enquire about AEs. While patients receive acupuncture, AEs still may occur, such as pain, bleeding, fainting, infection, and hematoma. The rate of incidence will be carefully recorded in the case report forms, and the causality with acupuncture therapy will be analyzed.

### Data collection and management

Case report forms (CRFs) are designed to make data entry and export more convenient (55). Evaluators will record the detailed personal information and classify the research data of the subject in the CRFs. After the observed recourse end, CRFs will be sorted out in time and imported into the electronic database. To ensure the security and accuracy of databases, the completed paper CRFs will be collected into locked cabinets uniformly. In addition, the electronic database is managed by a third-party person who does not involve in the research process, so the researcher cannot modify the data content. Participants will be identified by a code and their personal information will be hidden and kept strictly confidential. The Data Monitoring Committee of the Rehabilitation Center of the First Affiliated Hospital of Guangzhou University of TCM aims to monitor the trial progress regularly, make sure the safety of the trial, and verify the completeness of the CRFs.

### Statistical analysis

#### Clinical data analysis

Third-party statisticians who do not involve in the whole assignment process and implementation of the trial will be invited to conduct statistical analysis. The data will be analyzed using SPSS 26.0 software (SPSS, Inc., Chicago, IL, USA) according to the intention-to-treat principle. The multiple imputation-expectation maximization algorithms are conducted to impute missing data. Continuous variables are summarized as mean ± standard deviation (SD) and tested using a *t*-test or Wilcoxon rank-sum test analysis. Categorical variables are reported in percentage (%) and compared using Pearson's *X*^2^ test or Fisher's exact test. The groups' comparisons are analyzed by *t*-test (independent *t*-test for comparison between the groups; paired *t-*test for comparison within the same group). The non-parametric Wilcoxon rank-sum test or the Mann-Whitney U test will be conducted for the measurement data without a normal distribution or homogeneous variance. All bilateral hypothesis tests with a significance level <0.05 will be considered statistically significant.

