### Sample size

The sample size was calculated by the primary outcome. According to the results of preliminary pre-experiment, the Mean ± SD of HAMA score in patients who received conventional therapy plus JTNT was 14.25 ± 7.10, while it was 19.46 ± 4.80 in patients who received conventional therapy plus sham acupuncture. Statistical power is set at 0.90, alpha is set at 0.05, and two-sided tests are performed. After calculations performed by PASS 15.0 (NCSS LLC. Kaysville, Utah, USA) software, 30 people are estimated for each group. The estimated loss to follow-up rate is 20%, so each group will eventually need to include 38 people. The formula for sample size calculation is as follow. Therefore, to verify the placebo effect of sham acupuncture, a waiting group was recruited. The number of participants in the waitlist control group is equal as the sham acupuncture group. Finally, a total of 114 participants will be randomly divided into three groups in the proportion of 1:1:1.

(1)
$$\begin{array}{l} N=\frac{{\left(Z_{\alpha }+Z_{\beta }\right)}^{2}*2\sigma^{2}}{\delta^{2}} \end{array}$$

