### The primary outcome

The primary outcome is the change in the performance of anxiety symptoms, which is estimated by the 14-item Hamilton Anxiety Rating Scale (HAMA-14) and the 7-item Generalized Anxiety Disorder scale (GAD-7).

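### Arms are compared by tests that ignore the baseline score, and within-arm paired tests stand beside them as group comparisons, although baseline HAMA is measured in everyone

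*Protocol article*

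**What the plan says.** The Clinical data analysis section states that group "comparisons are analyzed by *t*-test (independent *t*-test for comparison between the groups; paired *t-*test for comparison within the same group"). For non-normal data or unequal variances it substitutes Wilcoxon or Mann-Whitney tests. It names no baseline covariate and no longitudinal model. Covariates appear only under MRI data analysis, for the correlations between imaging and scales.

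The primary outcome section says: "The primary outcome is the change in the performance of anxiety symptoms", measured by HAMA-14 and GAD-7. Table 1 schedules both scales, and NIHSS and MBI, at baseline and at weeks 2, 4, 8, 12 and 16. Entry requires a HAMA score from 14 to 28.

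The Sample size section uses pilot HAMA scores: "the Mean ± SD of HAMA score in patients who received conventional therapy plus JTNT was 14.25 ± 7.10". For the sham arm it gives a mean of 19.46 with SD 4.80. It adds: "Statistical power is set at 0.90, alpha is set at 0.05, and two-sided tests are performed". It concludes that "30 people are estimated for each group" and, after allowing for 20% loss, arrives at 38 per arm.

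**The concern.** There are three linked issues.

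- **Unused baseline.** The baseline value of each scale is collected in everyone at no extra cost and probably predicts the later value. A test that ignores it, or that simply subtracts it, generally leaves more residual variance than one that adjusts for it.
- **Within-arm tests.** Patients enter above a HAMA threshold, 2 weeks to 3 months after a stroke, and all receive routine drugs and rehabilitation. Any arm can improve through recovery and regression to the mean. A significant paired test in the JTNT arm is therefore not evidence for JTNT, and a significant result in one arm with a non-significant one in another is not a test of the difference. The article lists these tests as group comparisons under the same 0.05 threshold and does not mark them as descriptive.
- **Score versus change.** The powered quantity is a score and the named outcome is a change. The two have different SDs unless the baseline to follow-up correlation happens to take one particular value.

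**Working it through.** **Inputs from the Sample size section.** HAMA 14.25 (SD 7.10) for JTNT and 19.46 (SD 4.80) for sham; two-sided alpha 0.05; power 0.90; 20% loss. These must be scores and not reductions: read as reductions, the larger value would favour sham.

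**Assumed, not in the article.** Baseline HAMA SD (SDb) of 3.5 to 4.3; a uniform spread over the 15 integer scores from 14 to 28 gives sqrt((15² − 1)/12) = 4.3. Baseline to follow-up correlation r of 0.2 to 0.6.

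**Step 1: the plan's own figure.**
- Difference = 19.46 − 14.25 = 5.21.
- SD = sqrt((7.10² + 4.80²)/2) = 6.06; standardised effect = 5.21/6.06 = 0.86.
- Normal approximation: n = 2 × ((1.960 + 1.282) × 6.06/5.21)² = 28.4. The t-based solution is 29.4, so 30 per arm.
- Power at 30 per arm: 0.906 (0.904 with a Welch test and unequal SDs).
- Dropout: 30/0.80 = 37.5, so 38; 3 × 38 = 114.

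The plan's numbers reproduce, as a calculation on raw scores.

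**Step 2: the alternatives at 30 per arm.** Difference 5.21, noncentral t, two-sided 0.05.
- SD of change = sqrt(6.06² + SDb² − 2 × r × 6.06 × SDb).
- Residual SD under ANCOVA = 6.06 × sqrt(1 − r²).

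| r | ANCOVA SD (power) | Change, SDb 3.5: SD (power) | Change, SDb 4.3: SD (power) |
|---|---|---|---|
| 0.2 | 5.94 (0.916) | 6.36 (0.877) | 6.69 (0.842) |
| 0.3 | 5.78 (0.930) | 6.02 (0.909) | 6.29 (0.884) |
| 0.4 | 5.55 (0.947) | 5.66 (0.939) | 5.86 (0.923) |
| 0.5 | 5.25 (0.966) | 5.27 (0.964) | 5.40 (0.957) |
| 0.6 | 4.85 (0.984) | 4.85 (0.983) | 4.89 (0.982) |

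**Step 3: reading the table.**
- The change score is noisier than the raw score when r < SDb/(2 × 6.06), that is below 0.29 (SDb 3.5) or 0.35 (SDb 4.3). Because 30 per arm gives slightly more than 0.90 on the raw score, change-score power drops under 0.90 a little lower, at about 0.27 and 0.34.
- Three of the ten change-score cells are below 0.90. No ANCOVA cell is.
- The variance penalty of change against ANCOVA is 18% at r = 0.3 and SDb 4.3, since (6.29/5.78)² = 1.18. At r = 0.5 it is 1% (SDb 3.5) to 6% (SDb 4.3).

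**The case against.** The between-arm t-test, on score or on change, is unbiased after randomisation, and its standard error already allows for chance baseline imbalance. ANCOVA improves efficiency and does not repair an error. This stands, and the point is one of precision.

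The power argument rests on two unstated quantities, and most of the grid favours the plan: seven of ten change-score cells exceed 0.90. The figure of 30 per arm also presumes the full 20% loss. This stands too. The article does not say whether the between-arm test is on the score or the change; if it is on the end-of-treatment score, the power calculation matches the analysis.

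A reader might infer that the trial is underpowered, that the analysis is a fixed series of separate t-tests at every visit, or that the paired tests will carry the efficacy claim. The article supports none of these. No SD of change or correlation is given, the visits to be tested are not stated, and the Introduction's hypothesis is a comparison with sham.

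A journal article condenses a fuller plan, and model detail is commonly left there. But the article names the tests, so an analysis plan would have to depart from them to bring in the baseline. A mixed model with unstructured covariance for every scale would be a preference, not a necessity.

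**Conclusion.** The concern holds as a recommended improvement. The named tests leave baseline information unused, and within-arm tests appear as group comparisons although they cannot isolate the effect of JTNT. That second part depends on no assumed number.

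Under the assumed baseline SD and correlation, ANCOVA gives power 0.92 to 0.98 at 30 per arm, against 0.906 for the raw score and 0.84 to 0.98 for the change score. The gain over the change score is largest at low r and almost vanishes at r = 0.6. The sample size is arithmetically correct for a raw-score comparison. Whether 0.90 holds for a change-score test depends on r, with a shortfall below roughly 0.3 to 0.35 in the assumed range of baseline SD.

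**What to change.** - Make the JTNT-sham comparison of HAMA baseline-adjusted: ANCOVA on the post-treatment score with baseline HAMA as covariate. A mixed model for repeated measures with baseline as covariate is an option.
- Do the same for the other outcomes that have a baseline value (GAD-7, NIHSS, MBI, ACTH, CORT), checking the distribution of each.
- Label within-arm before/after tests as descriptive and not evidence of efficacy.
- State that the planned power refers to the end-of-treatment HAMA score, after confirming that the pilot values were taken then, which the Sample size section does not say. Add that the baseline-adjusted analysis of that score is, in large samples, at least as powerful.

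The cost is a few lines of wording. No new patients or data are needed, and the planned SPSS software can fit these models.

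### The non-parametric fallback names one independent-sample test twice, offers no rank test for the paired comparisons, and treats unequal variance alone as a reason to leave the comparison of means

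*Protocol article*

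**What the plan says.** All of the test rules are in the Clinical data analysis section of the protocol article.

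- Continuous variables are to be "tested using a *t*-test or Wilcoxon rank-sum test analysis".
- Group comparisons then split into an independent t-test between groups and a "paired *t-*test for comparison within the same group".
- The fallback follows directly: "The non-parametric Wilcoxon rank-sum test or the Mann-Whitney U test will be conducted for the measurement data without a normal distribution or homogeneous variance".

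No signed-rank test, other paired rank test or Welch t-test is named anywhere in the article. No test of normality or of equal variance is named either.

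The Sample size section takes its inputs from a pilot. For the active arm, "the Mean ± SD of HAMA score in patients who received conventional therapy plus JTNT was 14.25 ± 7.10"; the sham arm had a mean of 19.46 and an SD of 4.80. It adds: "Statistical power is set at 0.90, alpha is set at 0.05, and two-sided tests are performed". From these, "30 people are estimated for each group", raised to 38 for 20% loss, which gives 114 over three groups.

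**The concern.** There are two separate faults in one sentence.

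**Paired data.** The fallback has to replace two parametric tests, one unpaired and one paired, but it offers a single unpaired test under two names. A before/after comparison of non-normal data would then be tested as if the two sets of values came from different patients. When the values within a patient are positively correlated, the rank-sum test uses too large a variance. It rejects too rarely and misses real within-group change.

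**Unequal variance.** The rule makes lack of homogeneous variance, by itself, enough to move to a rank test. Unequal spread does not call for ranks, because Welch's t-test handles it and still compares means. When spreads differ, the rank-sum test no longer has a simple reading as a shift in location. The sample size rests on a difference in mean HAMA, so the tested quantity could change according to a preliminary look at the trial data.

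**Working it through.** **1. The plan's own sample size.** Inputs from the Sample size section: means 14.25 and 19.46, SDs 7.10 and 4.80, two-sided alpha 0.05, power 0.90.

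- δ = 19.46 − 14.25 = 5.21
- σ² = (7.10² + 4.80²)/2 = (50.41 + 23.04)/2 = 36.725, so σ = 6.06
- N = (1.960 + 1.282)² × 2 × 36.725 / 5.21² = 28.4, rounded up to 29 by the printed normal formula
- With the t distribution, power is 0.896 at 29 and 0.906 at 30 per group (Welch: 0.894 and 0.904), so 30 is the first size to reach 0.90
- 30 / 0.80 = 37.5, so 38; 3 × 38 = 114

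The stated 30, 38 and 114 reproduce from a t-test. The trial is therefore sized on a difference in means.

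**2. Rank-sum test on paired data.** The article gives no before/after correlation r, so r = 0.3, 0.5 and 0.7 are assumed. For bivariate normal data in large samples, pairing multiplies the variance of the rank-sum statistic by (1 − ρ), where ρ = (6/π) arcsin(r/2) is the rank correlation. The true type I error is then 2[1 − Φ(1.96/√(1 − ρ))].

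| r | ρ | 1.96/√(1 − ρ) | Formula | Simulated, n = 30 | Simulated, n = 38 |
|---|---|---|---|---|---|
| 0.3 | 0.288 | 2.32 | 2.0% | 2.0% | 2.0% |
| 0.5 | 0.483 | 2.72 | 0.6% | 0.6% | 0.6% |
| 0.7 | 0.683 | 3.48 | 0.05% | 0.1% | 0.1% |

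The simulations used 20,000 normal data sets. A separate simulation with lognormal data at n = 38 gave 2.1%, 0.9% and 0.2%. The signed-rank test stayed at 4.2 to 5.3% for the same correlations in the normal data.

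Power for an assumed change of 0.5 SD, normal data:

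| r | n | Rank-sum | Signed-rank |
|---|---|---|---|
| 0.3 | 30 | 0.44 | 0.59 |
| 0.5 | 30 | 0.44 | 0.74 |
| 0.7 | 30 | 0.43 | 0.92 |
| 0.3 | 38 | 0.56 | 0.70 |
| 0.5 | 38 | 0.57 | 0.83 |
| 0.7 | 38 | 0.60 | 0.97 |

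**3. How often the variance trigger would fire.** The pilot variance ratio is 50.41/23.04 = 2.19. The article names no variance test, so three are shown, each at 5% on normal data with the pilot SDs.

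| Variance test | 30 per group | 38 per group |
|---|---|---|
| Levene, mean-centred | 48% | 59% |
| Levene, median-centred | 44% | 55% |
| F test (exact) | 54% | 65% |

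**4. What the switch costs between groups.** Same SDs, 20,000 runs.

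| | Mann-Whitney | t-test | Welch |
|---|---|---|---|
| Type I error, n = 30 | 5.3% | 5.2% | 5.1% |
| Power, n = 30 | 88.7% | 90.6% | 90.5% |
| Type I error, n = 38 | 5.3% | 5.1% | 5.1% |
| Power, n = 38 | 94.8% | 96.1% | 96.0% |

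A two-stage rule (Levene, then t-test or Mann-Whitney) held type I error at 5.1% at both sizes. Against Welch, the rank test loses 90.5 − 88.7 = 1.8 points at 30 per group and 96.0 − 94.8 = 1.2 points at 38.

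**The case against.** The strongest reply is that this is a slip of wording. The sentence just before the fallback separates independent from paired t-tests, so the authors know the difference, and a pair of rank tests would make sense if rank-sum stood for signed-rank. The article also never expressly assigns either rank test to the within-group comparison. This may well be right. But the same section says rank-sum in two places and signed-rank nowhere, so the text has to be corrected whichever reading was meant. Nor is this a detail left to an analysis plan: the article does name the tests.

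The second reply is that the main question is untouched. The hypothesis and the sample size concern JTNT against sham, so the within-group tests are supportive, and a conservative test adds no false positives. Both points stand, and they limit the weight of the paired fault.

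The third reply concerns the variance rule. With equal arms the switch hardly changes type I error or power, and arm means and SDs would still be reported whichever test gives the p-value. That also stands. A reader might infer from the trigger rates that the primary analysis is compromised in about half of trials. The documents do not support that. The rates show how often the test might change, not harm done; they rest on a variance test that the article does not name; and the pilot SDs are of HAMA scores, whereas the primary outcome is a change judged on HAMA-14 and GAD-7, for which no SD is given.

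**Conclusion.** The point holds as a correctable fault in the stated rule. As written, non-normal before/after data have no suitable rank test. Using the named one would bring a nominal 5% test down to roughly 2% at r = 0.3, under 1% at r = 0.5 and 0.1 to 0.2% at r = 0.7. At 38 per group and r = 0.5 it would cut power for a 0.5 SD change from 0.83 to 0.57. The correlations, the size of change and the data shapes are assumptions. A reader might call these tests invalid in the sense of producing false claims, but with positive correlation the error runs the other way. The article gives no distribution for any outcome, so how often the non-normal branch would be used is unknown.

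The variance trigger is a poor rule with small consequences. It could plausibly apply to HAMA scores (44 to 65% over three variance tests and two group sizes, normal data, pilot SDs taken as true). It moves the test off the mean difference used for the sample size, at a cost of about 1 to 2 points of power and almost no change in type I error.

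**What to change.** Replace the fallback sentence with three statements:

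- For within-group comparisons of non-normal data, use the Wilcoxon signed-rank test.
- For non-normal data in independent groups, use the Mann-Whitney U test, named once, noting that it is the same test as the Wilcoxon rank-sum.
- For between-group comparisons of means, use Welch's t-test, fixed in advance, so that unequal variance does not lead to a rank test.

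Bring the section's other mention of the rank-sum test into line with this. The change is one or two sentences and needs no further patients, visits or data. The sample size is unaffected: Welch's t-test has power 0.904 at 30 per group with the pilot figures.

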#### MRI data analysis

The DPARSF software platform (DPARSF, Data Processing Assistant for rs-fMRI, GNU GENERAL PUBLIC LICENSE, Beijing, China) is used to preprocess the MRI data, based on the Resting-State fMRI Data Analysis Toolkit (REST; http://www.restfmri.net) and the statistical parametric mapping (SPM8; http://www.fil.ion.ucl.ac.uk/spm). Then, the rs-fMRI data corrections are performed on the images such as slice timing and realignment for intra-volume acquisition delay. To minimize the influence of head movement, subject with head motion (maximum displacement > 2.5 mm or angle movement > 2°) during the whole fMRI scan will be excluded. Stabilization of the magnetization and adaptation of the participants to the fMRI environment will take time. For each time series, the first 10 time points will be deleted to exclude non-neuronal BOLD noise signals (59). In spatial normalization, the whole brain template of the Montreal Neurological Institute (MNI) standard space is normalized in all data spaces (isotropic voxel size = 3 × 3 × 3 mm) (60). By calculating Kendall's coefficient of concordance (KCC), a voxel-by-voxel basis of a given voxel time series with its neighboring 26 voxels is generated to obtain a separate ReHo map. Finally, a spatially smoothed function with 4 × 4 × 4 mm (full width at half maximum) Gaussian kernel is applied to reduce the noise and residual in the gyrus anatomy. The statistical analysis tool of REST is performed for independent *t*-tests to identify the ReHo patterns of the three groups (61). Besides, a paired *t*-test is applied to compare the changes in the brain before and after the treatment in each group. Covariates, such as age and education, are considered by the Pearson correlation coefficient to analyze the relationship between the improvement scores of the correlation scales and the brain regions of fMRI image data.

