Resting-state functional magnetic resonance imaging (rs-fMRI) is an effective and non-invasive technique to record the activity of the brain in various neuropsychiatric disorders including PSA (34–36). It is revealed that the main regions related to anxiety effects are hippocampus, thalamus, frontal lobe, amygdala, insular cortex, and prefrontal cortex (37–40). The hypothesis of our study is to explore the underlying neural mechanisms of PSA through blood-oxygen-level-dependent effects (41). Regional homogeneity (ReHo) is used to process the fMRI images (42). To evaluate resting-state brain activity effectively, Kendall's coefficient of concordance (KCC) is used to compare a given voxel's time series with its nearest neighbors (43). ReHo theory states that in an area where ReHo is increased, the connections between neurons are strengthened. Conversely, the presence of reduced ReHo indicates a weakening of local connections between neurons. ReHo has shown to be a highly sensitive and reliable method for determining the regional activity level of each voxel in the brain of a single individual (44). Yet, few studies have investigated how acupuncture modulates brain regions in patients with PSA using fMRI. As a result, we use rs-fMRI to explore the possible changes in brain activity and try to find the associations among brain activity, disease activity, and anxiety statuses. This study provides preliminary neurophysiological evidence for the potential efficacy effect of acupuncture on PSA.

In recent years, JTNT has increasingly attracted the attention of clinicians and researchers. However, there is insufficient evidence about the real effects of JTNT on PSA patients. Therefore, we hypothesize that acupuncture will have better clinical efficacy than sham acupuncture in clinical symptoms, anxiety degree, and quality of life. We try to investigate the potential mechanism by enzyme-linked immunosorbent assay (ELISA) and rs-fMRI.

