This trial attempted to assess possible mechanisms of JTNT for PSA by the HPA axis. To dynamically observe the therapeutic effect of acupuncture on PSA, we detected the key factors of the HPA axis–the changes in ACTH and CORT before and after treatment. The action mechanism of JTNT is investigated by functional magnetic resonance imaging (fMRI) to observe whether JTNT can relieve anxiety symptoms by activating the core brain regions associated with emotion regulation.

However, this study still has limitations. First, this is a single-center study, because of the COVID-19 outbreak, we cannot conduct trials in multiple centers. Secondly, due to the use of a new type of acupuncture equipment in this study, it is necessary to explain to the patient well in exchange for greater compliance. In addition, we are still working hard to standardize the process of this study to provide high-quality medical evidence for JTNT so that it can be used as an optimized plan for PSA supplementation therapy.

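### The brain-symptom correlation carries no treatment-arm term, so if it is run across arms it can be significant with no link between ReHo change and improvement within any arm

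*Protocol article*

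**What the plan says.** The MRI data analysis section of the protocol article describes three steps on the ReHo maps. Independent t-tests compare the groups. A paired t-test "is applied to compare the changes in the brain before and after the treatment in each group". A Pearson correlation, with age and education given as example covariates, is then used "to analyze the relationship between the improvement scores of the correlation scales and the brain regions of fMRI image data".

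The paired test is stated group by group; the correlation names no group. The scales and the brain regions are not listed. The Introduction reports that "the main regions related to anxiety effects are hippocampus, thalamus, frontal lobe, amygdala, insular cortex, and prefrontal cortex", but as background, and nothing ties those regions to this analysis. The Discussion says the imaging is to show "whether JTNT can relieve anxiety symptoms by activating the core brain regions associated with emotion regulation".

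**The concern.** In a randomised trial, two variables that both respond to treatment are correlated in the pooled sample even when they are unrelated among patients on the same treatment. The arm means alone produce the association. A correlation of improvement with ReHo across all patients therefore mixes two questions: whether the arms differ on both variables, and whether patients whose ReHo changed more also improved more. The group comparisons already address the first. Only the second speaks to a patient-level link.

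This correlation is the only planned analysis that connects ReHo with anxiety relief in the same patients. If it is pooled and turns out significant, it is likely to be read as support for the mechanism described in the Discussion, when treatment effects on each variable separately would be enough to explain it.

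**Working it through.** **Inputs from the Sample size section.** "Statistical power is set at 0.90, alpha is set at 0.05, and two-sided tests are performed"; "Mean ± SD of HAMA score in patients who received conventional therapy plus JTNT was 14.25 ± 7.10"; "it was 19.46 ± 4.80 in patients who received conventional therapy plus sham acupuncture"; "30 people are estimated for each group".

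**The plan's own figure.**
- Difference: 19.46 − 14.25 = 5.21.
- Pooled SD: √[(7.10² + 4.80²)/2] = 6.06.
- Standardised effect: 5.21/6.06 = 0.86.
- Normal formula: 2(1.960 + 1.282)²/0.86² = 28.4, so 29 per group. The t-test needs 30 (power 0.896 at 29, 0.906 at 30).
- Allowing for 20% loss: 30/0.80 = 37.5, so 38 per group and 114 in total.

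The sample size reproduces, and this point does not touch it. The article gives no figure for the correlation.

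**Assumptions.**
- The within-arm correlation is exactly zero.
- The HAMA effect is d_x = 0.86. It comes from HAMA scores and stands in for improvement scores, because no SD of change is given.
- The ReHo effect d_y is not in the document; 0.5, 0.8 and 1.0 SD are examined.
- There are 30 evaluable patients per arm. The head-motion exclusion could lower this; full retention would give 38.
- In the three-arm case, waitlist equals sham on both variables.

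**Expected pooled correlation.** With a share p of patients on JTNT and q = p(1 − p),

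r = q·d_x·d_y / √[(1 + q·d_x²)(1 + q·d_y²)],

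where q = 1/4 for two equal arms and 2/9 for three. For two arms and d_y = 0.8: r = 0.172/√(1.185 × 1.160) = 0.147. For three arms: r = 0.153/√(1.164 × 1.142) = 0.133.

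**Chance of p < 0.05.** By Fisher's z, with z = atanh(r)·√(N − 3), the chance is Φ(z − 1.96) + Φ(−z − 1.96). For two arms and d_y = 0.8, N = 60, z = 1.116 and the chance is 20.0%. Simulation with 20,000 runs per setting agrees:

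| ReHo effect (SD) | Two arms: r | Fisher z | Simulated | Three arms: r | Fisher z | Simulated |
|---|---|---|---|---|---|---|
| 0 | 0 | 5% | 5% | 0 | 5% | 5% |
| 0.5 | 0.096 | 11% | 11% | 0.086 | 13% | 13% |
| 0.8 | 0.147 | 20% | 21% | 0.133 | 24% | 24% |
| 1.0 | 0.177 | 27% | 28% | 0.160 | 33% | 33% |

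With 38 per arm, the simulated rates for 0.5, 0.8 and 1.0 SD are 13%, 24% and 34% (two arms) and 14%, 29% and 41% (three arms).

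**After removing arm means.** The same test on arm-centred data is significant in 4.7% to 5.3% of runs in every setting at 30 per arm.

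**Choice of regions.** If a region is taken forward because JTNT and sham differ on it at p < 0.05, the pooled test is significant in 11% to 16% of such cases with no true ReHo effect (30 per arm). At 0.8 SD, selection adds little: 23% to 26%, against 21% to 24% without it (two arms, or three with waitlist equal to sham). Adjusting for arm does not deal with multiplicity. Six independent regions on one scale at 0.05 give 1 − 0.95⁶ = 26% chance of at least one false positive.

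**The case against.** The strongest reply is that the article never says the arms are pooled. The sentence before works group by group, so a within-arm correlation is compatible with the text and would have no such bias. The covariate list is open, so arm is not ruled out. A reader might infer that pooling is the stated plan; it is not. It is the likelier reading, because the group restriction appears on the paired test and is absent from the correlation.

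A reader might also infer that the regions will be picked from the group maps, making the correlation circular. The document does not say so, and the Introduction's list could equally supply an advance set. Region definitions are also the kind of detail a condensed article leaves to a fuller document. Both points stand, so selection is only a possibility to guard against.

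The size rests on a ReHo effect that the document does not give and on scores used in place of change scores. Where treatment shifts both variables, the pooled correlation is truly non-zero; it is a false positive only as evidence of a within-arm link. The Introduction presents the association aim as exploratory. These points limit the size and importance of the concern but do not remove it: the article does choose an estimator and name covariates, and an estimator that includes arm answers the patient-level question under either reading.

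**Conclusion.** The point holds in limited form. As written, the correlation has neither an arm term nor a within-group restriction. Run across arms, it would be significant in about 11% to 28% of trials (two arms) or 13% to 33% (three arms, waitlist equal to sham) with no within-arm association, against 5% after adjustment. These figures assume 30 per arm, a HAMA effect of 0.86 SD taken from scores, and a ReHo effect of 0.5 to 1.0 SD. With no ReHo difference between arms and no selection of regions on that difference, there is no inflation.

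It would go too far to say that the pooled correlation mostly restates the difference between arms. The expected r is only about 0.09 to 0.18, and most simulated trials in these settings are not significant. What is at stake is the interpretation of an exploratory mechanism analysis. The primary anxiety comparison and the sample size are unaffected.

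**What to change.** In the MRI data analysis section, replace the plain Pearson coefficient with a partial correlation, or a linear regression of HAMA-14 change on ReHo change, that includes treatment arm together with age and education. The sentence needs rewording in any case, since a plain Pearson coefficient cannot carry covariates.

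Fix the regions before unblinding, drawing them from those named in the Introduction. Resolve the overlap between frontal lobe and prefrontal cortex so that the masks are distinct, and apply a Holm correction across them. Report correlations in any region picked from the group comparison as descriptive.

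The cost is a change of wording and a short extra analysis of data already being collected. Arm takes two degrees of freedom: with 90 evaluable patients, and age and education each entered as one term, 90 − 6 = 84 residual degrees of freedom remain. The correlation may come out smaller. Even adjusted for arm, it would show association and would not by itself prove that ReHo change brings about the relief of anxiety.
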